## Abstract

**Background:**

Children in Lao People’s Democratic Republic (Lao PDR) receive suboptimal nutrition because of low breastfeeding rates, undermining their developmental potential. While major public health campaigns have attempted to increase breastfeeding rates, they have been largely unsuccessful. One explanation for these unsuccessful interventions is the economic and financial constraints faced by mothers. A potential solution for alleviating these pressures is providing social transfers to support breastfeeding; defined as a cash or in-kind transfer. Capitalizing on key strategies used in previous social transfer programs, we will assess the effectiveness of social transfer intervention for increasing exclusive breastfeeding rates in Vientiane, Lao PDR.

**Objective:**

This study aims to conduct a randomized controlled trial (RCT) designed to assess whether social transfers can increase exclusive breastfeeding rates in Vientiane Capital, Lao PDR.

**Methods:**

A prospective, parallel cluster-RCT was conducted among 300 mothers who recently gave birth and initiated breastfeeding. Enrolling 100 participants for each intervention arm provided us with 80% power to detect an increase in exclusive breastfeeding from the anticipated 21% in the control arm to 40% in either of the 2 intervention arms. Mother-infant dyads were enrolled at approximately 1 month post partum. Follow-up visits will occur at 6 months, 1 year, 2 years, and 3 years post partum; with the ambition to extend the follow-up period. Mother-infant dyads were enrolled between August 2022 and April 2023 with follow-up until 3 years post partum (2026). A local study team comprised of 2 nurses and 2 laboratory technicians is responsible for enrollment and follow-up of participants. Participants were randomly assigned to one of three groups during the baseline, 1-month visit: (1) control group, no social transfer; (2) intervention group 1, an unconditional social transfer at 6 months post partum; and (3) intervention group 2, a social transfer at 6 months post partum conditional upon mothers exclusively breastfeeding. All groups received educational materials supporting mothers to exclusively breastfeed. The primary end point will be exclusive breastfeeding at 6 months post partum. Secondary end points will include exclusive and complementary breastfeeding duration, childhood wasting and stunting, child growth, maternal and infant stress, predictors of early breastfeeding cessation, intestinal inflammation, anemia, maternal weight loss, maternal blood pressure, maternal anxiety, and GRIT personality score. Questionnaires and physical examinations were used to collect information.

**Results:**

As of November 2023, the study has enrolled 300 participants. Study participation is ongoing until December 2026 at minimum. Over the study lifetime, 93% have completed all visits.

**Conclusions:**

We see potential for a long-term program that may be implemented in other low- or lower-middle-income countries with only minor modifications. The RCT will be used as a basis for observational studies and to investigate the impact of human milk on child fecal microbiota and growth.

**Trial Registration:**

ClinicalTrials.gov NCT05665049; https://clinicaltrials.gov/study/NCT05665049

**International Registered Report Identifier (IRRID):**

DERR1-10.2196/54768

## Introduction

Breastfeeding provides important benefits for infants and societies [1,2]. Despite its well-known and widespread benefits, breastfeeding rates remain low in many parts of the world. In Vientiane, the capital of Lao People’s Democratic Republic (Lao PDR), only 21% of children aged 0-5 months were exclusively breastfed, and less than half (42.3%) were predominantly breastfed in 2017 [3]. Complying with the World Health Organization’s breastfeeding recommendations can help countries meet the United Nation’s sustainable development goals with respect to good health and well-being, economic growth, and reduced inequalities [4].

Even though most mothers recognize the benefits of breastfeeding, they also face a complex web of factors that make breastfeeding difficult, including formal labor commitments without sufficient parental leave or breastfeeding support, and television ads promoting infant formula [5,6]. Over the last 30 years, the Ministry of Health in Lao PDR has attempted to increase breastfeeding rates through standard public health behavior change campaigns, including a safe motherhood program and a large United Nations children’s fund supported exclusive breastfeeding promotion campaign; however, these programs were largely unsuccessful [5].

One probable explanation for these unsuccessful interventions is the economic and financial constraints faced by mothers. A potential solution for alleviating these pressures is providing social transfers to support breastfeeding; defined as a cash or in-kind transfer. Evidence suggests that social transfers have helped increase breastfeeding rates in other settings. In a previous experiment, Puerto Rican mothers were provided US $25 per month after successful observation of breastfeeding (ie, conditional cash transfer), which resulted in significantly higher breastfeeding rates at 6 months postpartum compared with mothers who did not receive the cash transfer [7]. A similar model providing a social transfer with a letter encouraging mothers to spend time with their infant (ie, labeled social transfer) in a US neonatal intensive care unit increased the daily provision of breastmilk [8]. However, all evidence on social transfer programs for breastfeeding comes from high-income countries. In fact, no study has implemented a social transfer program for breastfeeding promotion in low- or middle-income countries despite a large number of successful social transfer programs targeting other health behaviors in these settings [9].

Capitalizing on key strategies used in previous social transfer programs, we will assess the effectiveness of social transfer programs for increasing breastfeeding rates in Vientiane, Lao PDR. A previous qualitative, community-engaged project in Vientiane focused on identifying breastfeeding norms and social transfers that would support breastfeeding mothers (unpublished data). Using the results from this study, we designed a culturally grounded social transfer program that is responsive to the identified needs of new mothers.

The overall objectives of this project are to assess (1) the effect of social transfers on exclusive and complementary breastfeeding duration and (2) the long-term impacts of breastfeeding on child development.

## Methods

### Overview

The Social Transfers for Exclusive Breastfeeding (STEB) is a prospective, parallel cluster-randomized trial in the Vientiane Capital, of Lao PDR. Mother-infant dyads will be enrolled at approximately 1 month post partum and followed for 3 years; with the ambition to extend the follow-up period. The study period runs from August 2022 to December 2026.

### Participants and Recruitment

Our study is nested within an ongoing birth cohort (the Vientiane Multigenerational Birth Cohort [VITERBI]). Women were recruited for VITERBI if they (1) lived in one of the following districts of Vientiane: Chanthabuly, Sikhottabong, Sangthong, or Mayparkngum; (2) had an expected due date/or gave birth between July 1, 2022, and June 30, 2023; (3) did not plan to permanently move outside the study area; (4) did not have a medical, intellectual, or psychological disability; and (5) agreed to participate and sign an informed consent; if younger than 18 years, a legal representative had to agree to sign the informed consent.

The target sample size for the STEB randomized control trial was 300 mothers and their children. All pregnant women enrolled in VITERBI were eligible to participate in our study if they gave birth within the last 4 weeks, were exclusively breastfeeding at the time of recruitment, had no illnesses that contraindicate breastfeeding, and had a healthy singleton infant of 37 weeks or more gestation with a birth weight of at least 2500 g.

A local study team comprised of 2 nurses and 2 laboratory technicians was responsible for enrollment and follow-up of participants. Using pregnancy records from VITERBI, a list of potential participants was created. In order to identify women who recently gave birth (≤1 month), the following data were used: (1) approximate due date or (2) weeks gestation when an approximate due date was not provided. When both variables were missing, the average week of gestation was set at 40 weeks and added to the interview date to provide the latest possible birth date. All potential participants were screened on a telephone call to ensure they met the eligibility criteria. If the participant met the inclusion criteria and agreed to participate in the study, a baseline visit was scheduled.

### Sample Size Calculation and Power

Enrolling 100 participants for each intervention arm provided us with 80% power to detect an increase in exclusive breastfeeding from the anticipated 21% in the control arm to 40% in either of the 2 intervention arms.

### Study Logistics

During the baseline visit, if informed consent was given, a random number was generated within the Open Data Kit (ODK) platform that assigned the mother to a control or intervention group. If they were randomly assigned to an intervention group, mothers were allowed to choose from the following social transfers: (1) money (US $75); (2) developmental toys, clothes, and diapers for the child; or (3), a combination of money and developmental toys, clothes, and diapers for the child (Figure 1). We created a shopping catalog with different toys and clothes for them to choose from. At the end of the visit, the study team encouraged intervention group 1 to meet their breastfeeding goals and told them that the social transfer would be provided at 6 months post partum to show our support for their breastfeeding efforts. Mothers randomly selected for the third intervention arm were told that they would only receive their social transfer if they exclusively breastfed and nurses could observe breastmilk expression at the 6-month visit. All intervention and control groups received educational material about the benefits and recommendations of exclusive breastfeeding.

During a follow-up visit when the child is 6 months of age, nurses will collect an end-line survey from mothers, collect infant fecal samples, and observe breastmilk expression.

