### Outcomes

The primary end point will be exclusive breastfeeding at 6 months postpartum. Secondary end points will include exclusive and complementary breastfeeding duration, childhood wasting and stunting, child growth (height and weight), maternal and infant stress, predictors of early breastfeeding cessation, intestinal inflammation, anemia, maternal weight loss, maternal blood pressure, maternal anxiety, and GRIT personality score.

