STEB has some limitations worth noting. The small sample size will prohibit more nuanced data analysis. Enrollment does not occur immediately after birth; instead, all participants are enrolled at 1-month post partum. Many mothers face significant barriers to exclusive breastfeeding during the first month postpartum; therefore, the study population of STEB may be slightly different. Recall of the exact timing of complementary foods provided is likely biased; yet, previous research has shown that recall bias for breastfeeding is minimal.

STEB was designed to provide a unique platform to investigate the short- and long-term impacts of exclusive and complementary breastfeeding on child health and development. Further, the longitudinal sampling of human milk and infant feces provides a unique opportunity to study human milk as a biological system and how this impacts the gut microbiome. If proven effective, we see potential for a long-term program that may be implemented in other low- or lower-middle-income countries with only minor modifications.

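### Only the conditional arm is rewarded for reporting exclusive breastfeeding, and observed milk expression cannot confirm exclusivity, so both contrasts with that arm can be inflated by misreporting

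*Protocol article*

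**What the plan says.** All references are to the Protocol article.

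- **Endpoint (Outcomes):** "The primary end point will be exclusive breastfeeding at 6 months postpartum". No rule for ascertaining it is given there.
- **Data at 6 months (Study Logistics; Endline—6 Months Postpartum):** nurses survey the mother, take infant stool and watch for milk expression. The infant-feeding items are in the survey. Stool, milk and saliva samples are collected, but none is given a role in classifying exclusivity.
- **Conditional arm (Study Logistics):** mothers were told at baseline that "they would only receive their social transfer if they exclusively breastfed and nurses could observe breastmilk expression at the 6-month visit". The transfer is US $75, goods, or a mix of the two.
- **Unconditional arm (Study Logistics):** mothers were told that "the social transfer would be provided at 6 months post partum to show our support for their breastfeeding efforts", with no condition on feeding.
- **Control arm (Abstract, Methods):** "control group, no social transfer".
- **Planned effect (Sample Size Calculation and Power):** "80% power to detect an increase in exclusive breastfeeding from the anticipated 21% in the control arm to 40% in either of the 2 intervention" groups.
- **Reporting error (Discussion, limitations):** the article accepts that recalled timing of complementary foods is probably biased, then adds that "previous research has shown that recall bias for breastfeeding is minimal". It does not mention reporting influenced by the transfer.

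**The concern.** A mother in the conditional arm who also gives formula, water or solids but is still lactating can pass the expression check. Whether she receives the transfer then depends on what she says about exclusivity. Mothers in the other two arms gain nothing from either answer. Misclassification can therefore differ by arm, and in the conditional arm it runs in the direction of benefit. A larger sample does not remove such a bias.

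The trial asks whether a conditional transfer changes feeding. Without some way to gauge false reports, a positive conditional-arm result cannot separate changed feeding from changed reporting. The same applies to any finding that the conditional transfer works better than the unconditional one.

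**Working it through.** **Inputs.** Control rate 21%, target 40% and 80% power come from Sample Size Calculation and Power. Arm size is 100: that section says "Enrolling 100 participants for each intervention arm", and Participants and Recruitment gives a total target of 300, which leaves 100 controls. A two-sided 5% level and independent mothers are assumed; the article states no significance level.

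**1. The plan's own figure.** Pooled two-proportion formula with p̄ = 0.305:

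n = [1.96·√(2·0.305·0.695) + 0.842·√(0.21·0.79 + 0.40·0.60)]² / 0.19² ≈ 91 per arm, or 102 with continuity correction. The stated 100 is reproduced within tolerance. Without the correction, power at 100 per arm is 83.6%.

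**2. Misreporting with no true effect.** Let p be the true rate in every arm and m the share of non-exclusive conditional-arm mothers who report exclusivity, in excess of any such reporting in control. Then:

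reported rate = p + (1 − p)·m; apparent gain = (1 − p)·m.

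At p = 21%, 100 per arm:

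| m | Reported rate, conditional | Apparent gain (points) | Chance of a significant result |
|---|---|---|---|
| 5% | 25.0% | 4.0 | 10% |
| 10% | 28.9% | 7.9 | 25% |
| 15% | 32.9% | 11.9 | 47% |
| 20% | 36.8% | 15.8 | 70% |
| 24.1% | 40.0% | 19.0 | 84% |

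The full planned gain needs m = 0.19/0.79 = 24%.

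**3. Other true rates (assumed).** Every enrolled mother was exclusively breastfeeding at recruitment, so the true 6-month rate may exceed 21%. Required m = 0.19/(1 − p):

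- p = 30%: 0.19/0.70 = 27%
- p = 40%: 0.19/0.60 = 32%
- p = 50%: 0.19/0.50 = 38%
- p = 60%: 0.19/0.40 = 48%

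**4. Allowing for the expression check.** Only mothers still lactating can pass it. If a share L of non-exclusive mothers is lactating (assumed), the required false-report share among them at p = 21% is 0.19/(0.79·L):

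- L = 90%: 27%
- L = 70%: 34%
- L = 50%: 48%

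With both adjustments, at p = 40% and L = 70%: 0.19/(0.60·0.70) = 45%.

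**5. Misreporting common to all arms.** If 10% of non-exclusive mothers misreport in control as well, and the conditional arm adds a further 24.05 percentage points, the reported rates are 28.9% and 47.9%. The chance of a significant result is 79%. Misreporting shared by the arms changes little; the excess drives the bias.

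**6. Tipping point.** This needs no true rate, only observed counts. z = (p₂ − p₁)/√(2·p̄·(1 − p̄)/100), with 21 of 100 reporting exclusivity in control:

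- 40 in conditional: 0.19/√(2·0.305·0.695/100) = 2.92
- 34 in conditional: 0.13/√(2·0.275·0.725/100) = 2.06, still significant
- 33 in conditional: 0.12/√(2·0.27·0.73/100) = 1.91, not significant

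So 40 − 33 = 7 false answers among the 40 (17.5%) would remove significance.

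**The case against.** The strongest reply has four parts.

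- **Ascertainment is inferred.** A reader might infer that the article defines the endpoint as self-report. It does not: Outcomes gives no ascertainment rule, and Study Logistics does not say how nurses decide that a mother exclusively breastfed. The full protocol, which is not shown, may add a check. This stands as a limit. Still, the survey is the only source on exclusivity described, and the one-arm payment rule is stated outright.
- **24% is near the low end.** This stands. The 21% is a population figure for children aged 0–5 months (Introduction), mothers who have stopped lactating gain nothing from a false answer, and only misreporting in excess of control counts. The documents give no misreporting rate, so a reader who infers that misreporting will produce the planned effect goes further than they allow. They support only that it can.
- **The recall remark is about something else.** A reader might take it as dismissing reporting error for the primary contrast. The sentence concerns the timing of complementary foods and itself calls that recall likely biased. The fair criticism is that reporting driven by the transfer is not mentioned, and that the remark does not cover it.
- **Later data cannot settle the matter.** The 1-year questionnaire covers infant feeding, but the article does not say whether it can reconstruct 6-month status. Recall would be noisier, and a mother may repeat her earlier answer, so agreement would not prove truth. This stands, and it limits that comparison to a supporting role.

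None of these removes the one-arm incentive or shows that expression verifies exclusivity.

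**Conclusion.** The concern holds for conditional versus control and conditional versus unconditional. Unconditional versus control, one of the two comparisons against control in the power statement, is not exposed to this mechanism. The direction of the possible bias is clear; its size is not.

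With no true effect, reproducing the whole planned gain would take excess false reporting by one of the following:

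- about 24% of non-exclusive conditional-arm mothers at a true rate of 21%;
- 27–48% of them at assumed true rates of 30–60%;
- 27–48% of those still lactating, at a true 21%, if 90–50% of non-exclusive mothers are lactating (assumed).

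A merely significant result needs less: at a true 21%, a reported 34% takes 0.13/0.79 = 16%. The significance calculations rest on a two-sided 5% test, 100 independent mothers per arm and no check on exclusivity beyond those described.

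**What to change.** 1. Pre-specify, for the two conditional-arm contrasts, a tipping-point analysis using the same test as the primary analysis. Report the excess number and share of conditional-arm yes answers that would have to be false to remove significance (in the example above, 7 of 40, or about 18%).
2. Describe the conditional-arm result as an effect on reported exclusive breastfeeding, with the tipping point shown beside it. No pass mark is needed; readers can judge whether that share is plausible.
3. If the 1-year infant-feeding module allows it, compare discordance between the 6-month and 1-year answers by arm, as supportive evidence only.
4. State in the limitations that the recall remark on complementary foods does not cover reporting influenced by the transfer.

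This needs no new data and no change to the intervention. The cost is a small amount of extra analysis and a more cautious claim for the conditional arm.

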**Figure 1 figure1:**
[figure not shown]
Screenshot from shopping catalog for Social Transfers for Exclusive Breastfeeding (STEB) participants.

### Data Collection Instruments

#### Overview

STEB has a total of five questionnaires: (1) a screening questionnaire to assess eligibility; (2) baseline enrollment conducted at approximately 1 month post partum; (3) an endline questionnaire at 6 months post partum; (4) a follow-up visit at 1 year post partum; and (5) a follow-up visit at 2 years post partum. All source documents were created in English and translated into Lao. We briefly describe each questionnaire below.

#### Screening Questionnaire

A screening questionnaire was conducted on the telephone in order to assess the inclusion and exclusion criteria. A maximum of 10 questions were asked. If an answer to one of the questions rendered them ineligible for the study, no further questions were asked. Questions included date of birth and expected birth date in order to determine prematurity of the infant, birth parity, birthweight, current breastfeeding status, breastfeeding exclusivity, long-term medical problems of the infant, and if the mother experiences galactosemia, human immunodeficiency virus, human T-cell lymphotropic virus type 1 or 2, illicit drug use (ie, cocaine), Ebola, artificial breast implants, or infectious tuberculosis.

#### Baseline—1 Month Postpartum

The baseline questionnaire is conducted at approximately 1 month post partum and includes employment questions, the short Grit scale [10], family and gender roles, child health and vitamin, mineral or other medicine intakes, breastfeeding and infant feeding, Breastfeeding Self-Efficacy Scale–short form [11], and maternal diet. The Demographic and Health Surveys household characteristics questionnaire. Hemoglobin levels of the mother and infant were taken using the HemoCue Hb 301. Biospecimen samples included infant feces, human milk, and a saliva sample from the mother and infant. Anthropometric measurements of the child included skinfold thickness of the triceps, subscapular, quadriceps, and flank, weight, length, mid-upper arm circumference (MUAC), and head circumference. Anthropometric measurements of the mother included skinfold thickness of the triceps, subscapular, quadriceps, and flank, blood pressure, height, weight, and heart rate.

#### Endline—6 Months Postpartum

The endline questionnaire is conducted at approximately 6 months post partum and includes employment questions; child health; vitamin, mineral, or other medicine intake; breastfeeding and infant feeding; maternal diet; participation in cultural postpartum activities (eg, hotbeds and mother roasting); perceived stress scale [12]; Postpartum Specific Anxiety Scale [13]; and caregiver-reported early development instruments [14]. A variety of additional health measurements were assessed. Hemoglobin levels of the mother and infant were taken using the HemoCue Hb 301. Biospecimen samples include infant feces, human milk, and a saliva sample from the mother and infant. Anthropometric measurements of the child included skinfold thickness of the triceps, subscapular, quadriceps, and flank, weight, length, MUAC, and head circumference. Anthropometric measurements of the mother included skinfold thickness of the triceps, subscapular, quadriceps, and flank, blood pressure, height, weight, and heart rate.

